### Participants

The diagnosis of spinal cord injury is based upon decreased superficial and deep sensation in the lower limbs, genitals and perinea area, decrease voluntary motor movement in lower limbs, and impaired urinary and anal sphincter control.

### Neurologic Evaluation

Motor and sensory examinations are performed at admission to the acute hospital, preoperatively, immediately after surgery, and 6 weeks, 6 months, 12 months, and at the most recent follow-up.

Outcome is measured by using the American Spinal Injury Association ASIA summed motor and sensory scores [29] and the NASCIS [4,5] system to score neurological status and motor and sensory function.

Patients are to be assigned an initial motor index score from 50 to 100 which includes manual muscle test scores of all key muscles, sensory examination of pin prick and touch, sacral and deep tendon reflexes, and muscle tone evaluation. Sensory level is recorded as the most caudal dermatomal level of bilateral intact sensation.

### Inclusion criteria

Participants are eligible if they are 18 years or older, have a spinal cord injury between T1 and L1 of traumatic etiology, are hemodynamically stable, have spinal cord compression on MRI and are between 0 hours and 24 hours post-injury.

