### Exclusion criteria

Subjects with major and current psychiatric illness, who have significant traumatic brain injury associated with the spinal cord injury, major concurrent medical disease (including myocardial infarction within 3 months, uncompensated congestive heart failure, active systemic cancer, AIDS, diabetes mellitus), pre-injury major neurologic deficits or disease (e.g. stroke, Parkinson's disease, syringomyelia, Guilian-Barre), ankylosing spondylitis, penetrating injuries to the thoracolumbar, pregnant females, life-threatening injuries which prevent early decompression of the spinal cord, criminals, under indictment or incarceration, substance abuse, an ASIA Impairment Scale category of E, no cord compression on MRI, the presence of spinal shock, any cognitive deficit, unable to provide informed consent, and an injury which involves more than two adjacent vertebral levels. Selected participants are thoroughly informed of the trial and its attendant risks and asked to consent to be in one of two groups, those operated urgently in less than 24 hours from trauma or the late group who are operated and decompressed between 24 and 72 hours from trauma.

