### Ethics

RCTs raise a number of ethical issues specifically related to the timing in the study design. If a patient has a potential chance of improvement by an early surgical decompression, it is ethically unacceptable to limit his/her access to this treatment. In both "early" and "late" decompression groups, everything including facilities and managements will be exactly the same except the time of decompression.

At first glance, the "difference" in chance of improvement between "early" and "late" groups seems unethical per se. During a group discussion we came to an agreement that what makes this RCT ethically unacceptable is not the above mentioned "difference" but withholding patients who could potentially benefit from early treatment. As the benefit of the timing of surgery is unclear and the timing of surgery in developed countries may be delayed as long as 4 or 5 days, delayed surgical intervention of greater that 24 hours is not an ethical concern. In developed countries, only 24% of SCI patients have access to a hospital setting that may provide early decompression surgery within the first 24 hours of injury [30]. This proportion is much less in developing countries because of lack of fundamental resources. [27]. We decided to set up a rapid response surgical team consisting of the same personnel providing regular care to SCI patients. When a SCI patient is referred to the hospital, he/she will randomly gets assigned into either the "early" or "late" treatment group. In the case of the "late" group, we will not interfere with the regular medical care process during the first 24 hours. If a patient comes to the hospital and he/she gets an "early" code, then the rapid response team will be summoned and the patient will be prepared for early surgery. We will not let the patient wait due to financial reasons, waiting lists, etc. All other interventions for rescue, resuscitation, hemodynamic stabilization, transport, imaging study, and surgical preparation will be provided in a standard way according to the guidelines of the hospital. Surgical, paramedical and nursing teams will be the same for both groups. Patients of the "early" group will benefit from the routine care provided for all other patients before and after surgery.

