### Early and late surgically decompressed group

The patients will be divided into two groups: Early (less than 24 hours from trauma) and late (between 24 and 72 hours following SCI). Because surgical technique varies according to the location of injury in the spine and the nature of the injury, surgeons are not restricted in their surgical technique. Radiographic parameters are evaluated on admission and post-operative images are done to assess the adequacy of decompression. Imaging studies are reported as soon as possible after the decompressive procedure but within a maximum of 7 days post treatment to assess the adequacy of the treatment.

Rehabilitation regimes start from the first day of trauma in all of the patients. Complications are identified and presented.

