### Clinical Significance

We will consider a result significant if there is a 5-point or greater improvement in the summed ASIA motor score beyond what would be expected analyzing recovery in the setting of spinal cord injury [31]. It means that anyone who demonstrates a 5 point improvement will be classified as "improved'. We intend to conduct logistic regression on those who improve using the ASIA scale.

Intention to treat analysis will be used.

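### The entry window and the early-surgery limit both end 24 hours after injury, so patients enrolled near the limit can be allocated to early surgery they cannot receive in time, which dilutes the intention-to-treat contrast

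*Protocol article*

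**What the plan says.** All references are to the Protocol article.

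- **Inclusion criteria:** patients are eligible if they "are between 0 hours and 24 hours post-injury". They must also be haemodynamically stable and have cord compression on MRI.
- **Early and late surgically decompressed group:** the arms are "Early (less than 24 hours from trauma) and late (between 24 and 72 hours following SCI"). The consent description under Exclusion criteria uses the same clock for the early arm: "those operated urgently in less than 24 hours from trauma".
- **Ethics:** "When a SCI patient is referred to the hospital, he/she will randomly gets assigned into either the 'early' or 'late' treatment group". For a patient with an early code, "then the rapid response team will be summoned and the patient will be prepared for early surgery". Allocation Concealment likewise has the envelope opened when the patient is referred.
- **Exclusion criteria:** the only exclusion tied to whether early surgery can be done is life-threatening injury that prevents it. Late arrival is not mentioned.
- **Clinical Significance:** "Intention to treat analysis will be used".
- **Data Collection and Statistical analysis:** the intervals from trauma to admission and from admission to operation are both recorded.

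**The concern.** Eligibility and the early-arm definition are both timed from injury and both end at 24 hours, with no margin between them. A patient enrolled shortly before that hour is eligible for randomisation, but only one of the two allocations can still be delivered. If the code is late, the patient complies without difficulty. If it is early, surgery falls after the limit. The failure arises in one arm only, and the entry rule itself creates it.

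Under intention to treat such a patient stays in the early arm, which is correct, but contributes an outcome under later surgery. The early-arm response rate then moves toward the late-arm rate. Timing is the only thing this trial compares, so poor separation of achieved times weakens its one question. A small observed difference could mean that timing matters little, or that many early-arm patients were not operated early.

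**Working it through.** **1. The time limits side by side**

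| Item | Clock starts | Limit |
|---|---|---|
| Eligibility | injury | 24 h |
| Early surgery | injury | under 24 h |
| Late surgery | injury | 24 to 72 h |
| Randomisation | at referral | no check of time left |

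The margin between the last eligible hour and the early-surgery limit is 24 − 24 = 0 hours. For a patient enrolled at the end of the window, early surgery is impossible. Earlier in the window it depends on the time from arrival to theatre, which the article does not give.

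**2. The plan's own sample size**

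Inputs from Sample size: 33% (early) v 9% (late), 80% power, 5% error, 149 per group. Two-sided testing is assumed, since the article does not say.

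n = [1.96 √(2p̄(1 − p̄)) + 0.8416 √(p1(1 − p1) + p2(1 − p2))]² / (p1 − p2)²

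With p̄ = 0.21: (1.1290 + 0.4633)² / 0.24² = 2.535 / 0.0576 = 44.02, so 45 per group. The stated 149 is not reproduced. That is a separate matter, but it explains the power results below. The allowance for loss does reproduce: 298 × 1.10 = 327.8, or 328.

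**3. Dilution**

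Let c be the share of the early arm operated after 24 hours, and assume those patients respond at the late-arm rate:

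early-arm rate = 0.33 − c × (0.33 − 0.09); difference = 24 × (1 − c) points.

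Power with n = 149 per group is Φ{[d√n − 1.96 √(2p̄(1 − p̄))] / √(p1(1 − p1) + p2(1 − p2))}, where d is the diluted difference and p1 and p̄ are recomputed for each c.

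| c (assumed) | Early-arm rate | Difference (points) | Power at 149 per group |
|---|---|---|---|
| 0 | 33.0% | 24.0 | 99.9% |
| 10% | 30.6% | 21.6 | 99.8% |
| 20% | 28.2% | 19.2 | 99.1% |
| 30% | 25.8% | 16.8 | 97.2% |
| 40% | 23.4% | 14.4 | 92.5% |
| 50% | 21.0% | 12.0 | 83.0% |
| 60% | 18.6% | 9.6 | 67.3% |

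Power reaches about 80% when the early-arm rate falls to about 20.5%, that is at c = (33 − 20.5)/24 ≈ 0.52.

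**4. How far the power result can be relied on**

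The cushion exists because 149 is well above the 45 that 33% v 9% needs. If the true undiluted effect were only about 20.5% v 9% (an assumption, chosen because 149 per group detects it with 80% power), power would be 73%, 64% and 54% at c = 10%, 20% and 30%.

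**The case against.** The case on the other side has real weight.

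- **Patients may already be imaged and stable at entry.** The inclusion criteria require both, so it cannot be assumed that these steps remain to be done after enrolment. This stands as a caution. It does not close the gap: if imaging comes first, the clock has simply run further before the envelope is opened. Neither order includes a check of the time left.
- **The rapid response team.** The Ethics section provides one for early-coded patients and rules out waiting for financial reasons or lists. This shortens delay after arrival and should keep c down. It cannot recover hours already spent.
- **The Background defends 24 hours as realistic.** It cites transport and MRI to explain why 8 hours is hard to meet, so it should not be read as saying that 24 hours usually fails. Infeasibility is certain only close to the limit.
- **The dilution formula is severe.** A patient operated just after 24 hours may do better than the late arm as a whole, which extends to 72 hours. If benefit declines gradually, 24(1 − c) overstates the loss.

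Three stronger readings are tempting, and the article does not support them.

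- **Regrouping by achieved time.** A reader might infer this from the sentence dividing patients by time from trauma. That sentence names the arms; allocation is by envelope and analysis by intention to treat.
- **Late-arm patients operated early.** A reader might infer this from "we will not interfere with the regular medical care process during the first 24 hours". But the late arm is defined as 24 to 72 hours, patients consent to that window, the principal investigator checks that the allocation is followed, and the Ethics section describes surgery within 24 hours as uncommon in usual care.
- **Too few patients.** On the stated rates, the planned 149 per group covers dilution up to about half of the early arm.

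**Conclusion.** The point holds in a limited form. The entry limit and the early-surgery limit coincide, nothing before randomisation checks that early surgery is still possible, and the resulting non-receipt falls on the early arm only. The intention-to-treat contrast is therefore attenuated toward no difference.

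The amount is unknown, because it depends on arrival times and arrival-to-theatre times that the article does not report. The shares in the table are illustrations, not estimates, and they give an upper bound on dilution if benefit declines gradually with time. On the plan's own response rates the consequence is mainly a smaller and less interpretable estimate of the timing effect; loss of power is not the main concern. The gap is worth closing because it bears directly on the primary question and costs little to remove.

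**What to change.** Reconcile the Inclusion criteria, the Ethics account of randomisation at referral, and the definition of the arms:

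1. Add an entry condition ensuring that only patients for whom both allocations are still feasible are randomised. The sponsor should set it in advance; no time limit is proposed here.
2. Make the condition objective and identical for both arms, and have it checked and recorded before the envelope is opened. The plan already applies this principle when it excludes life-threatening injuries that prevent early decompression.
3. Report achieved injury-to-decompression time by randomised arm, as the sum of the two intervals already collected, so that readers can see how well the arms were separated.

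The cost is that some late arrivals are not enrolled, although they add little to a contrast of timing. The condition must leave no discretion to the attending who holds the envelopes. With fixed blocks of four at each site some allocations can be guessed, and a subjective judgement of feasibility would open a route to selective enrolment. No new data collection is needed beyond recording the entry check.

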### Exclusion criteria

Subjects with major and current psychiatric illness, who have significant traumatic brain injury associated with the spinal cord injury, major concurrent medical disease (including myocardial infarction within 3 months, uncompensated congestive heart failure, active systemic cancer, AIDS, diabetes mellitus), pre-injury major neurologic deficits or disease (e.g. stroke, Parkinson's disease, syringomyelia, Guilian-Barre), ankylosing spondylitis, penetrating injuries to the thoracolumbar, pregnant females, life-threatening injuries which prevent early decompression of the spinal cord, criminals, under indictment or incarceration, substance abuse, an ASIA Impairment Scale category of E, no cord compression on MRI, the presence of spinal shock, any cognitive deficit, unable to provide informed consent, and an injury which involves more than two adjacent vertebral levels. Selected participants are thoroughly informed of the trial and its attendant risks and asked to consent to be in one of two groups, those operated urgently in less than 24 hours from trauma or the late group who are operated and decompressed between 24 and 72 hours from trauma.

### Ethics

RCTs raise a number of ethical issues specifically related to the timing in the study design. If a patient has a potential chance of improvement by an early surgical decompression, it is ethically unacceptable to limit his/her access to this treatment. In both "early" and "late" decompression groups, everything including facilities and managements will be exactly the same except the time of decompression.

At first glance, the "difference" in chance of improvement between "early" and "late" groups seems unethical per se. During a group discussion we came to an agreement that what makes this RCT ethically unacceptable is not the above mentioned "difference" but withholding patients who could potentially benefit from early treatment. As the benefit of the timing of surgery is unclear and the timing of surgery in developed countries may be delayed as long as 4 or 5 days, delayed surgical intervention of greater that 24 hours is not an ethical concern. In developed countries, only 24% of SCI patients have access to a hospital setting that may provide early decompression surgery within the first 24 hours of injury [30]. This proportion is much less in developing countries because of lack of fundamental resources. [27]. We decided to set up a rapid response surgical team consisting of the same personnel providing regular care to SCI patients. When a SCI patient is referred to the hospital, he/she will randomly gets assigned into either the "early" or "late" treatment group. In the case of the "late" group, we will not interfere with the regular medical care process during the first 24 hours. If a patient comes to the hospital and he/she gets an "early" code, then the rapid response team will be summoned and the patient will be prepared for early surgery. We will not let the patient wait due to financial reasons, waiting lists, etc. All other interventions for rescue, resuscitation, hemodynamic stabilization, transport, imaging study, and surgical preparation will be provided in a standard way according to the guidelines of the hospital. Surgical, paramedical and nursing teams will be the same for both groups. Patients of the "early" group will benefit from the routine care provided for all other patients before and after surgery.

This design creates a "difference" in the potential chance of improvement among the two groups of patients by providing an "extra service" to one group rather than withholding the standard service from the other group. This solution may be a valid way of dealing with the ethical dilemmas associated with randomized controlled trials in SCI decompression.

All in all, to address the ethical problem in RCTs involving interference with the routine therapeutic process; it is suggested to provide extra services (in terms of speed or quality) to patients in clinical settings providing sub-optimal care.

The gap between medical care quality standards in developed and developing countries exits in many settings. This provides an opportunity for ethically acceptable RCTs in many health related fields which will result in a considerable addition to the medical science.

### Ethical approval

The trial approved by the ethics committees of the Sina Trauma and Surgery Research Center of Tehran University Medical Sciences and Shahid Beheshti University of Medical Sciences. The responsible ethics committees will monitor the trial.

### Informed consent

Written informed consent for this study will be obtained from the patient's authorized representative prior to the performance of any protocol-specific procedure. However, several of these assessments or tests may be performed as part of the patient's routine clinical evaluation (i.e. not specifically performed for this trial). The study will be conducted in accordance with the provisions of the Declaration of Helsinki, as amended in South Africa (1996).

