### Allocation Concealment

A batch of sealed, opaque sequentially number envelopes will be provided to the supervising attending at each site. Whenever a patient is referred to a hospital, his/her name will be printed on the envelope and then the envelope will be opened. The patient will then receive the treatment identified within the envelope. The principal investigator will supervise commitment to the randomization process by reviewing the names printed on the opened envelopes and insuring that the patient receives the recommended treatment.

Unbiased examiners who are not involved in the management of the patients will perform the examinations. Thus, the design of the study is single-blinded.

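### Eligibility is limited to adults who can consent for themselves, but the only written-consent rule names the patient's representative and not the patient

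*Protocol article*

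**What the plan says.** Four places in the protocol article bear on this.

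- Inclusion criteria: "Participants are eligible if they are 18 years or older". The same sentence requires that they "are between 0 hours and 24 hours post-injury".
- Exclusion criteria: the list removes patients with "any cognitive deficit, unable to provide informed consent". The section then ends: "Selected participants are thoroughly informed of the trial and its attendant risks and asked to consent to be in one of two groups".
- Informed consent: "Written informed consent for this study will be obtained from the patient's authorized representative", and this before any protocol-specific procedure. The section adds that some assessments may be done as routine care, and refers to the Declaration of Helsinki. It says nothing about the patient signing.
- Allocation Concealment: "Whenever a patient is referred to a hospital, his/her name will be printed on the envelope and then the envelope will be opened". No consent step is named there.

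**The concern.** A representative normally signs because the patient is a minor or lacks capacity. The eligibility criteria rule out both. Even so, the representative is the only person from whom written consent is to be obtained, and no condition is attached. A site that follows the Informed consent section to the letter could complete its paperwork without the signature of a patient who is able to decide.

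The decision in question is randomised timing of spinal surgery, and the Ethics section gives most of its argument to defending that allocation. Four hospitals take part, according to Limitations, and each would have to decide for itself which section governs. The matter therefore concerns protection of participants and uniform conduct across sites. It does not touch the estimand, the analysis or the power.

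**Working it through.** There is no figure to reproduce and no arithmetic applies. The check sets the sections side by side.

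1. *Who can be enrolled?* Inclusion criteria limit entry to adults. Exclusion criteria remove patients with a cognitive deficit or without the ability to consent. Together, every eligible patient is an adult able to give consent.

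2. *Who is asked?* The end of Exclusion criteria says that the participants are. This agrees with step 1.

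3. *Who signs?* Informed consent names the authorized representative alone. It neither offers the patient as an alternative signatory nor limits the representative to particular circumstances. This does not agree with steps 1 and 2.

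4. *Could some feature of the population explain step 3?* Minority and incapacity are excluded by step 1. Physical inability to sign is not the expected case: Participants describes the deficit in the lower limbs, the genital and perineal area and the sphincters. Associated injuries are recorded at enrolment, so an occasional patient might be unable to hold a pen. That would justify a conditional exception, but not a general rule.

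5. *Does another section settle it?* No. Ethics and Ethical approval do not say who signs. Allocation Concealment has the envelope opened when a patient is referred, without mentioning consent. Informed consent does require consent before any protocol-specific procedure, so the intended order can be inferred, but the randomisation text does not state it.

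The result is a contradiction in wording between Exclusion criteria (with Inclusion criteria) and Informed consent, which nothing else in the article resolves.

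**The case against.** The best defence is that the sections can be read together: the patient is informed and asked, and a representative supplies the written signature. The sentence does not say that the representative signs in place of the patient. It may also be a slip for wording that meant the patient or the representative. The article condenses a fuller protocol, consent pages are not available to us, two ethics committees approved the trial, and the Declaration of Helsinki is cited. One condensed sentence cannot show how consent is actually taken.

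Much of this stands. It rules out any claim that patients are not asked. It does not remove the contradiction. Condensing explains silence, but here the article makes a positive statement that conflicts with its own eligibility criteria. Even the presumed intended wording would leave open when a representative may act in a population that excludes people unable to consent.

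A reader might infer more, and the documents do not support it:

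- *That sedated or confused patients will be enrolled by proxy.* The consent section does not amend eligibility. The exclusion still applies, so this would require sites to breach it.
- *That the trial selects patients whose relatives arrive quickly, or loses time within the 24-hour window.* No section says that patients without a representative are turned away, and no time or rate is given. If consent precedes allocation, such selection would act on both arms alike and would not by itself bias the comparison between them.
- *That consent for the whole trial is invalid.* That is a legal conclusion with no basis in the article.

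**Conclusion.** The point holds as an inconsistency in a stated operating rule. The criteria restrict the trial to adults who can consent and say that they are asked, while the written-consent rule names only someone else. Taken literally, the rule can be met without the patient's signature.

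Its size cannot be measured from the documents. The rule as worded covers all 328 planned participants, but that is only the planned sample size. The article gives no number of patients who would be bypassed or missed, and does not show that any would be. The conclusion assumes that the sentence means what it says. If it is a drafting slip, the correction is the same. It is worth making because the text is plainly at odds with itself and the remedy is cheap, not because harm has been shown.

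**What to change.** Reconcile Informed consent with Exclusion criteria as follows.

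- State that written consent is obtained from the patient before allocation, and make the same order explicit in Allocation Concealment, so that the envelope is opened only after consent.
- State when, if ever, a representative may act, within what local law and the ethics committees allow. The article gives no basis for prescribing the details of that role here.
- State that a representative's consent does not make eligible a patient whom the Exclusion criteria remove.

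The cost is a sentence or two of amended text, a check of the consent form against it, and notification of the ethics committees. Sample size, study procedures and analysis are unaffected.
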